#### (1) MoCA-BJ

The MoCA- BJ scale is one of the Chinese versions of the Montreal cognitive assessment used to assess the general cognitive function [20], which has high sensitivity and specificity for screening cognitive impairment from patients with stroke [21].

#### (2) TMT

The trail marking test (TMT) was firstly used in 1944 for America army individual intelligence assessment [22]. Nowadays, it is widely employed as a diagnostic tool for visual attention and executive functioning and the processing speed for neuropsychological diseases [23, 24]. It consists of two parts in which the subject is instructed to connect a set of 25 circles containing numbers (Part A) or numbers and letters (Part B) arrayed pseudorandomly on a letter-size sheet of paper as fast as possible while still maintaining accuracy.

#### (3) ADL

The basic activities of daily living are assessed with the modified Barthel Index (MBI) [25], which is used to assess the individual self-care performance and derived from the Barthel index [26]. In this study, we used the Chinese version of MBI [27], it also consists of ten items: personal hygiene, bathing, feeding, toileting, stair climbing, dressing, bowel control, bladder control, ambulation or wheelchair and chair-bed transfer with total 100 scores indicating completed independence. The instrumental activities of daily living are evaluated with the Lawton Instrumental Activities of Daily Living Scale (LIADL) [28], which is consists of eight items: ability to use telephone, shopping, food preparation, housekeeping, laundry, mode of transporation, responsibility for own medications, ability to handle finances with higher scores representing more independent.

#### (4) SS-QOL

The Stroke-Specific Quality of Life Scale (SS-QOL), the first health-related QOL measure for stroke patients, was made available in 1999 [29]. It consists of 12 domains, 78 items with total 390 scores indicating a quality of life and is commonly used to evaluate the treatment methods, the rehabilitation programs and the burden of disease in stroke related studies [30].

#### (5) MRI scan and data preprocessing

MRI scanned on a 3.0 Tesla MRI system (GE Medical Systems, Waukesha, WI, USA) at the West China Hospital of Sichuan University. The structural MRI (High-resolution 3-demention T1-weighted, gradient echo, GRE) sequence (TR/TE = 8.5 ms/3.2 ms; flip angle = 12°; field of view = 256 × 256 mm^2^; matrix = 256 × 256; slice thickness = 1 mm; and 176 axial slices, scanning time = 4min33s) images were obtained with the same parameters in neuro-navigation. The resting-state functional MRI images were conducted with T2*- weighted Gradient echo—echo planar imaging (GRE-EPI) sequence (TR/TE = 2000 ms/35 ms; flip angle = 90°; field of view = 230 × 230 mm^2^; matrix = 64 × 64; slice thickness = 3.6 mm; and 35 axial slices, dummy samples = 5; statistical samples = 235, scanning time = 8 min) at pre- and post- treatment. When the fMRI scanning, the patients were required to close their eyes and keep awake and relax. All of the rs-fMRI data were preprocessed using Statistical Parametric Mapping (SPM8, http://www.fil.ion.ucl.ac.uk/spm) and Data Processing Assistant for Resting-State fMRI (DPARSF) [31]. Briefly, the volumes in the first 5 s were discarded for signal equilibrium. The remaining data were corrected for head motion. These data were then spatially normalized to the Montreal Neurological Institute (MNI) space and resampled to 3-mm isotropic voxels. We perform spatial smoothing with an 8 × 8 × 8 mm^3^ Gaussian kernel only for the ALFF analysis. Next, the linear trend of the data was removed, and temporal band-pass filtering (0.01–0.1 Hz, only for the functional connectivity (FC) analysis) was performed to reduce the effects of low-frequency drift and high-frequency physiological noise. Finally, six head motion parameters and three potential nuisance signals, including the cerebrospinal fluid, white matter and global signals, were removed from the time course of each voxel using multiple linear regression.

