#### (4) Sample size

Because no previous orthogonally designed study provides a significant difference of MoCA or MMSE scores for rTMS treatment to PSCI, which would allow us to accurately estimate the adequate sample size for this trial, we decided to recruit 45 PSCI patients who will be randomly divided into nine groups and three subgroups based on orthogonal design (5 patients per group, 15 patients per stimulating site subgroup), in consideration of the research grant, the recruitment feasibility and the recommended sample size in neuroimaging research (medians:14.5) [17].

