#### (6) ALFF and FC

The amplitude of low frequency fluctuation (ALFF) and functional connectivity (FC) will be used to explore different brain effects in the three stimulating -site subgroups.

The ALFF refers to the low frequency fluctuation of BOLD signal of the brain voxel, which will be calculated with DPARSF package after data preprocessing. The generated ALFF maps will be used for statistical analysis.

FC will be used to explore the functional connectivity changes in three brain networks (default mode network, DMN; dorsal attention network, DAN; central executive network, CEN) after treatment, which were obtained by meta-analysis (http://www.neurosynth.org/), were used as imaging indicators to analyze according to the methods described by Tomasi et al. [32]. First, Independent component analysis (ICA) will be used to extract DMN, DAN and CEN networks of the three groups, and then the brain regions with differences in the corresponding network will be found by visual observation, which will be used as regions of interest (ROI) to conduct Pearson correlation with the whole brain voxel. The FC maps obtained will be used for statistical analysis.

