### 4. Statistical analyses

The data of MoCA-BJ, TMT, MBI, LIADL and SS-QOL were shown as mean ± standard deviation (SD) and analyzed by the range analysis and one-way analysis of variance (ANOVA), which was used the SPSS 22.0 software (IBM, Armonk, NY, USA, 2020). The range analysis was used to determine the influence of each parameter at a specific level on the effect indicator and obtain the optimum combination of rTMS parameters. The one-way ANOVA was used to determine the statistical significance in nine different parameters’ combination of rTMS. P < 0.05 was considered significant.

For ALFF and FC maps, paired T-test will be used for intra-group comparison and one-way ANOVA analysis will be used for inter-group comparison in the three stimulating site subgroups. Then multiple comparison correction will be performed using Gaussian random field theory (GRF) with voxel *p* < 0.005, cluster *p* < 0.05. The Pearson correlation analyses were used to calculate the correlations between the changes in ALFF and FC with the clinical symptom scores at baseline and the end of the rTMS treatment (*p* < 0.05).

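### GRF cluster correction is applied to FC maps that the plan leaves unsmoothed, so the nominal 5% cluster error rate is not assured for FC

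*Protocol article*

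**What the plan says.** - **Preprocessing** (section 3, item (5) MRI scan and data preprocessing). Images are acquired with "field of view = 230 × 230 mm^2^; matrix = 64 × 64; slice thickness = 3.6 mm" and "resampled to 3-mm isotropic voxels". The 8 mm smoothing is limited: "Gaussian kernel only for the ALFF analysis".
- **FC maps** (section 3, item (6) ALFF and FC). Regions of interest are used "to conduct Pearson correlation with the whole brain voxel". The resulting maps go to statistical analysis, and no smoothing step is described in between.
- **Group tests** (section 4, Statistical analyses). "For ALFF and FC maps, paired T-test will be used for intra-group comparison", with one-way ANOVA across the three stimulating-site subgroups. Both kinds of map are then corrected by "Gaussian random field theory (GRF) with voxel *p* < 0.005, cluster *p* < 0.05".
- **Numbers** (section 1, item (4) Sample size): "15 patients per stimulating site subgroup".

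**The concern.** A GRF cluster p-value replaces the voxel grid by a smooth continuous random field, and takes the cluster-size threshold from a smoothness estimated on the residuals. The approximation is meant for maps that are several voxels smooth. For ALFF the plan supplies a kernel of 8/3 = 2.7 voxels. For FC it excludes that kernel, yet it relies on the same correction.

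FC in the default mode, dorsal attention and central executive networks carries the trial's mechanism aim. If the real cluster error rate is well above 5%, network findings may be false. If it is well below, real effects may be missed with 15 patients per subgroup.

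**Working it through.** **What can be reproduced.** The 5% is a nominal threshold. The document gives no smoothness or noise structure, so it cannot be recalculated directly. The check asks how the GRF rule behaves on null data built from the stated acquisition.

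**Inputs from the document.** In-plane resolution 230/64 = 3.59 mm; slice thickness 3.6 mm; 3 mm analysis voxels; n = 15; voxel p < 0.005; cluster p < 0.05.

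**Assumptions.** An ellipsoid mask of V = 72,141 voxels; noise generated at 3.6 mm and linearly interpolated to 3 mm; smoothness (FWHM, in voxels) estimated from the lag-1 correlation of the residuals. Sidedness and cluster connectivity are not stated, so one- and two-sided tests and 18- and 26-neighbour connectivity were all run.

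**Formulas.** With u the z-threshold:

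- Expected clusters: E(m) = V (4 ln 2)^1.5 (2π)^-2 (u² − 1) exp(−u²/2) / FWHM³
- Expected voxels above threshold: E(N) = V × 0.005 (one-sided)
- β = [Γ(5/2) E(m)/E(N)]^(2/3)
- Cluster p-value at size k: 1 − exp(−E(m) exp(−β k^(2/3)))

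**Numbers, one-sided.** u = 2.576 and E(N) = 72,141 × 0.005 = 360.7. At FWHM = 1.21 voxels (white native noise after interpolation), E(m) = 973, β = 2.34 and the 5% threshold is k = 8.6 voxels. The formula thus expects 973 clusters made from 361 voxels, which is impossible: the approximation is outside its range. At 1.66 voxels it still expects 377 clusters from 361 voxels. At 2.82 voxels (white noise after the 8 mm kernel) it expects 77, a coherent figure. This shows that the assumption is strained without smoothing, but not in which direction the error rate moves. That needs simulation.

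**Null simulation.** One-sample t-test on 15 difference maps, 400 runs per row. Threshold and mean largest cluster are for the one-sided, 18-neighbour variant; the error range covers all variants.

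| Assumed noise | FWHM (voxels) | E(m) | Threshold k | Mean largest null cluster | Cluster error (nominal 5%) |
|---|---|---|---|---|---|
| White native, unsmoothed | 1.21 | 973 | 8.6 | 5.0 | 1.0–1.8% |
| 6 mm intrinsic, unsmoothed | 2.17 | 169 | 37.1 | 18.1 | 0.5–0.8% |
| 80% short-range + 20% at 15 mm range, unsmoothed | 1.66 | 377 | 19.1 | 22.8 | 35–61% |
| White native, 8 mm smoothed | 2.82 | 77 | 69.6 | 31.1 | 0.5–0.8% |
| 80/20 mixture, 8 mm smoothed | 4.77 | 16 | 234.6 | 103.3 | 3.8–4.0% |

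The Monte Carlo standard error is about 0.5 percentage points near 1% and 2.5 points near 50%.

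**Second simulation.** Another run of the same kind (100 data sets per setting) gave about 2% for unsmoothed white noise, 19% for unsmoothed noise with a 20% long-range component, and 4% for the latter after 8 mm smoothing. Sign-flip permutation gave 3–7% throughout, but on only 30 runs per setting. The standard error at 5% is then √(0.05 × 0.95/30) = 4 points, so this is only a rough check.

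**Reading the results.** In the mixture, the lag-1 estimate is dominated by the short-range part. It understates the extent of the long-range part, and the threshold is set too low. With short-range noise alone, GRF is conservative with or without the kernel.

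**The case against.** **The plan may intend to smooth the FC maps later.** The preprocessing text is a summary, the FC method refers to a cited source, and an article may leave such steps to the full protocol. This is possible. But the text does not merely omit smoothing for FC: it confines the kernel to ALFF and then names FC under the same correction. As written, the two choices do not fit.

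**Smoothness is estimated from the data, so a protocol need not state it.** True, and its absence is no fault. The difficulty is that the estimate feeds an approximation that the unsmoothed maps may not satisfy.

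**A reader might infer that the true error rate is known to be far above 5%.** The document does not support that. A simulation with estimated smoothness of 0.8 voxel (150 data sets, 54,832 voxels) gave 45%, but resampling white noise from this acquisition to 3 mm gives 1.22 voxels with trilinear, 1.06 with cubic and 0.88 with nearest-neighbour interpolation, all above 0.8. The same simulation gave 0.7% at 1.4 voxels and 0% at 1.9. The 20–60% range rests on an assumed long-range component. It is plausible for network connectivity, but the document does not establish it.

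**A reader might also infer that smoothing restores 5%.** It does not under short-range noise, where the smoothed test stays below 1%.

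**The imaging results are secondary and exploratory.** This stands. MoCA-BJ, TMT and the choice of optimum parameters do not depend on this correction.

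**Conclusion.** The mismatch is in the text: GRF cluster correction is prescribed for FC maps that the plan leaves unsmoothed, so the nominal 5% cluster error rate is not assured for FC. Under assumed noise structures with n = 15, the rate runs from about 1–2% or slightly less (short-range noise, conservative) to about 20–60% (with a long-range component, inflated). No unsmoothed setting came close to 5%, but the document does not give the spatial structure that would decide between the two.

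The figures rest on an assumed mask, assumed noise mixtures and the lag-1 smoothness estimator. They cover only the paired test, not the three-site ANOVA. The point is worth correcting before analysis, and it concerns the secondary imaging outcome only.

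**What to change.** **Preferred.** In Statistical analyses, take FC cluster p-values from permutation: sign-flipping of the within-patient differences for the paired tests, and relabelling of patients for the three-site comparison. Keep voxel p < 0.005 as the cluster-forming threshold. This removes the reliance on smoothness.

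**If GRF is kept.** State that the FC maps are smoothed with the ALFF kernel before group tests, amend the preprocessing section to agree, and report the estimated smoothness with the results. This guards against inflation but may leave the test conservative.

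**Cost.** A short change of text and some computing time; if the maps are smoothed, slightly lower spatial resolution for FC.

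**What it does not solve.** Regions of interest are picked by eye from areas that already show differences. That is a separate threat to FC error control, and it remains whichever way the cluster p-values are obtained.

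### FC data are band-pass filtered before motion and nuisance regression, and nothing says the motion regressors get the same filter; the discarded 5 s also disagrees with five dummy volumes at TR 2 s

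*Protocol article*

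**What the plan says.** Section 3 (Outcomes), part (5) on the MRI scan and preprocessing, gives the steps in order.

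- Discard: "the volumes in the first 5 s were discarded for signal equilibrium".
- Realignment: "The remaining data were corrected for head motion". Normalisation follows, then smoothing for ALFF only.
- Detrending and filtering: "Next, the linear trend of the data was removed, and temporal band-pass filtering (0.01–0.1 Hz, only for the functional connectivity (FC) analysis) was performed".
- Nuisance regression, as the last step: "Finally, six head motion parameters and three potential nuisance signals, including the cerebrospinal fluid, white matter and global signals, were removed". These were "removed from the time course of each voxel using multiple linear regression".

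The same part gives the acquisition as "TR/TE = 2000 ms/35 ms" and "dummy samples = 5; statistical samples = 235, scanning time = 8 min".

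The section does not say whether the regressors themselves pass through the band-pass filter. FC change in three networks is part of a secondary outcome. Section 4 analyses it by paired t-tests within, and ANOVA between, the three stimulating-site subgroups, with Gaussian random field correction, and correlates it with clinical scores.

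**The concern.** Realignment precedes the filter, so the six motion parameters are broadband series unless someone filters them. Fitting a broadband series to band-limited data goes wrong in two ways. The coefficient is too small, because the out-of-band part of the regressor has no counterpart in the data. Subtracting the fitted term then adds that out-of-band part back with reversed sign, which undoes some of the filter's work. If seed and target voxel carry similar motion effects, what remains is common to both and they correlate falsely.

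Such a bias grows with head motion. If patients move more or less at the second scan, or if motion differs between the 15-patient site subgroups, it can look like an effect of rTMS on FC. The cluster correction controls multiplicity; it does not remove a systematic bias.

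The discard statement is a separate and smaller matter: a time of 5 s does not fit the other acquisition figures.

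**Working it through.** **Acquisition figures.** Inputs from part (5): TR 2 s, 5 dummy volumes, 235 analysed volumes, 8 min.

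- Scan time: (5 + 235) × 2 s = 480 s = 8 min. The stated figure is reproduced exactly.
- Five dummy volumes: 5 × 2 s = 10 s.
- The stated discard: 5 s / 2 s = 2.5 volumes, which is not a whole number. Dropping 2 or 3 of 240 leaves 238 or 237; only dropping 5 leaves 235. Taking 5 s off in addition to the dummies would leave 235 − 2.5 = 232.5.

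**What the written order does to one unfiltered regressor.** Let a voxel be signal plus w·m, where m is a motion series with a share φ of its variance inside the band, split as m = m_in + m_out.

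1. After the filter, the motion term is w·m_in.
2. Regression on unfiltered m gives a coefficient of about w·φ instead of w.
3. The residual motion is w(1 − φ)·m_in − wφ·m_out.
4. Relative to the motion variance that the filter let through, (1 − φ)² stays in band and φ(1 − φ) reappears out of band. The total left is 1 − φ.

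With 235 volumes at TR 2 s the frequency step is 1/470 Hz, and 43 of 117 non-zero frequencies lie in 0.01–0.1 Hz. For a flat spectrum φ = 43/117 = 0.368. Then 0.632² = 0.40 stays in band, 0.368 × 0.632 = 0.23 returns outside it, and 0.63 is left in total. If the regressor is filtered too, its whole variance is in band and nothing is left.

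**Check against simulation.** Settings: 235 volumes, TR 2 s, nine regressors all unfiltered, two voxels with independent in-band signals of SD 1, white noise of SD 0.7, a shared flat-spectrum artefact, 400 runs per setting.

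- In-band variance without motion: 1 + 0.49 × 0.368 = 1.18.
- Artefact 1 SD, no regression: 0.368 / (1.18 + 0.368) = 0.238. Simulated: 0.238.
- Artefact 1 SD, written order: 0.368 × 0.632 = 0.232, and 0.232 / (1.18 + 0.232) = 0.165. Simulated: 0.168.

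Across three assumed motion shapes (white, spiky, random walk), mean false r with a true correlation of 0 was:

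| Artefact, in signal SDs | Filter, then unfiltered regressors | Regress, then filter | Filter data and regressors |
|---|---|---|---|
| 0.5 | 0.02–0.05 | within 0.01 of 0 | within 0.01 of 0 |
| 1 | 0.09–0.17 | within 0.01 of 0 | within 0.01 of 0 |
| 2 | 0.23–0.43 | within 0.01 of 0 | within 0.01 of 0 |

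In the written order, 2–18% of the final variance lay outside the band.

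**Closer to the plan.** The cerebrospinal fluid, white-matter and global signals are already band-limited if they are taken from the filtered data. The open question is then mainly the six motion parameters. Further simulations used these three filtered signals plus six unfiltered motion series:

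- Artefact identical in every voxel: the global signal absorbs it, and false r is about 0.
- Artefact varying across the brain but shared by the tested pair or region: roughly 0.01–0.10 at 0.5 SD and 0.04–0.28 at 1 SD, depending on the assumed motion shape, its spread over the brain and the voxel noise.

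With the six motion series alone, the values are about 0.12 at 0.5 SD and 0.35 at 1 SD. That model omits three regressors the plan names, so it should not be taken as the size of the problem.

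**The case against.** The strongest reply is that the harm depends on something the article does not state. A reader might infer that the written order necessarily leaves motion in the data and creates false connectivity. The document does not support that. It is silent on whether the regressors are filtered, and with filtered regressors the same order gives a false correlation of about 0. The account is also an openly brief summary of a named software pipeline, so regressor handling may be set out elsewhere.

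Further points stand. Realignment is done before filtering, so only the regression of the motion parameters comes late. The global signal can absorb an artefact common to all voxels. No motion data are given, so every amplitude is assumed. A false pre–post change also needs motion, or its effect on the data, to differ between scans. FC is a secondary, exploratory outcome; the filter is not applied for ALFF; and MoCA-BJ, TMT and the choice of optimum parameters are untouched.

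This does not dispose of the point. The article states the order explicitly, regression last, and a literal reading allows the harmful version. When the artefact varies by region, the global signal does not rescue it.

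A reader might also infer from the 5 s that the wrong number of volumes will be analysed. The other figures agree on five dummies and 235 volumes, so this looks like a unit slip with no shown effect on any result.

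**Conclusion.** The point holds conditionally. As written, band-pass filtering precedes nuisance regression for FC, and nothing says that the motion regressors receive the same filter. If they do not, motion is only partly removed, out-of-band power returns and FC can be biased. With all nine regressors the false correlation runs from about 0 to roughly 0.10 at 0.5 SD and 0.28 at 1 SD. These values rest on assumed motion amplitude, shape and spatial pattern; they illustrate the risk and do not bound it. Either standard alternative brings the bias to about 0 in the same simulations. The consequence is confined to the FC results and the mechanism claims built on them.

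The 5 s statement is certainly inconsistent with TR 2 s and five dummy volumes, but it is editorial.

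**What to change.** For FC, state one of two pipelines:

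- detrend, regress out the six motion parameters and the three nuisance signals, then band-pass at 0.01–0.1 Hz; or
- apply the same 0.01–0.1 Hz filter to the data and to all nine regressors, and regress in one step.

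If the second is what the software already does, one sentence saying so is enough.

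Change the discard to the first 5 volumes (10 s), in agreement with TR 2 s, 5 dummy volumes, 235 analysed volumes and the 8 min scan.

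The cost is a change of step order or a clarifying sentence, plus one corrected figure. No new data are needed; any FC maps already produced with unfiltered motion regressors would have to be rerun.

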#### (6) ALFF and FC

The amplitude of low frequency fluctuation (ALFF) and functional connectivity (FC) will be used to explore different brain effects in the three stimulating -site subgroups.

The ALFF refers to the low frequency fluctuation of BOLD signal of the brain voxel, which will be calculated with DPARSF package after data preprocessing. The generated ALFF maps will be used for statistical analysis.

FC will be used to explore the functional connectivity changes in three brain networks (default mode network, DMN; dorsal attention network, DAN; central executive network, CEN) after treatment, which were obtained by meta-analysis (http://www.neurosynth.org/), were used as imaging indicators to analyze according to the methods described by Tomasi et al. [32]. First, Independent component analysis (ICA) will be used to extract DMN, DAN and CEN networks of the three groups, and then the brain regions with differences in the corresponding network will be found by visual observation, which will be used as regions of interest (ROI) to conduct Pearson correlation with the whole brain voxel. The FC maps obtained will be used for statistical analysis.

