## Discussion

As a non-invasive brain stimulation technique, the rTMS uses high intensity magnetic field pulses to modulate neural activity and in turn modifying the brain function. Over the past few decades, rTMS is widely applied into the cognition impairment due to many neurological, psychiatrical and psychological diseases, such as stroke, Alzheimer’s disease, Parkinson’s disease, schizophrenia, obsessive compulsive disorder. Several meta-analyses and RCT have showed that the safe and beneficial value of rTMS in cognitive function rehabilitation [10, 33–35]. Given the more and more application of this method in clinical and research settings, it is crucial to understand what is the optimal parameters of rTMS for cognition impairment and how the rTMS modulates brain function via the high intensity magnetic field pulses. Fortunately, some researchers have realized these two key points. Beynel L et al. thought that the rTMS parameters include a vast composition of spatial and temporal parameters: coil geometry, stimulation target, stimulation intensity; pulse waveform, pulse train frequency, number of pulses, etc [36]. while it does not be summed precisely from the perspective of clinical application. Based on the previous literature related to multiple sessions of rTMS for cognition impairment, we hold the opinion that the most important four parameters of rTMS are stimulating site, stimulating frequency, stimulating intensity and pulse number. Orthogonal design is a powerful method for comparative effectiveness research, especially for intervention with multiple parameters, it could significantly reduce the experiment numbers and alleviate the research workloads [37]. In rehabilitation medicine, many physical modalities are delivered with a specific equipment by presetting several parameters in the meantime. It is important that these parameters should be investigated at the same time when we are going to assess the efficacy and safety of this intervention. For example, the rTMS will be delivered to a patient with cognition impairment, the stimulating site, frequency, intensity and pulses should be predetermined meanwhile. However, in the previous studies, it was common that only one parameter, such as frequency, be compared with different level, or be compared between active and sham rTMS. It is not entirely and exactly consistent with clinical practice. Hence, in order to investigate the optimum parameters of clinical value of rTMS for post-stroke cognition impairment, the present study is designed orthogonally with L_9_(3^4^) orthogonal array based four parameters with three different level in each parameter (sites: DLPFC, IFG, TPC; frequency: 5Hz, 10Hz, 20Hz; intensity: 90%RMT, 100%RMT, 110%RMT; pulse number: 1000 pulses, 1500 pulses, 2000 pulses). On the other hand, although many studies showed that the modulatory effect of rTMS on brain function, ig. enhancing the neural activity and the connectivity between different brain regions [38], is correlated to the improvement of cognition function [39], the exact neurological mechanism has not been understanded very well. Giacomo Koch et al. showed that the rTMS stimulation on precuneus enhances memory and neural activity and connectivity in default mode network [40]. Recep A Ozdemir et al. Showed that the default mode network (DMN) and the dorsal attention network brain network (DMN/DAN) specificity of rTMS activations is correlated with cognitive performance in healthy volunteers [41]. Reza Kazemi et al. showed that the bilateral rTMS stimulation on DLPFC changes resting state in CEN, DMN brain networks and cognitive function in patients with bipolar depression [42]. However, whether the brain networks related to attention and executive function (CEN, DMN, DAN) is enhanced activity and connectivity and is correlated with the cognitive improvement following the rTMS stimulation in patients with post-stroke cognition impairment are still unclear. Therefor, in the current study, the amplitude of low-frequency fluctuation (ALFF) and the functional connectivity (FC) of the resting-state fMRI signal has been adopted to reflect the regional brain network (CEN, DMN, DAN) activity and connectivity and further our understanding of the complex cognitive function recovery process underlying metaplasticity with rTMS, demonstrate how the adaptive metaplasticity can contribute to the cognition impairment, and show that whether the maladaptive metaplasticity play a role in the cognitive pathophysiology [43].

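### Connectivity seeds are picked by eye where the trial's own networks look different and are then tested in the same patients, so the secondary connectivity results lean towards false positives

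*Protocol article*

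**What the plan says.** Methods 3(6), ALFF and FC, sets out a sequence for FC:

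1. "Independent component analysis (ICA) will be used to extract DMN, DAN and CEN networks of the three groups".
2. Then "the brain regions with differences in the corresponding network will be found by visual observation".
3. The regions so found are the ones "which will be used as regions of interest (ROI) to conduct Pearson correlation with the whole brain voxel".
4. "The FC maps obtained will be used for statistical analysis".

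The same paragraph also says of the three networks "which were obtained by meta-analysis (http://www.neurosynth.org/), were used as imaging indicators". It does not say how that source relates to the ICA and visual steps.

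Methods 4, Statistical analyses, tests the ALFF and FC maps by paired t-test within, and one-way ANOVA between, the three site subgroups, with GRF correction at voxel p < 0.005 and cluster p < 0.05. A separate sentence plans Pearson correlations of "the changes in ALFF and FC with the clinical symptom scores at baseline and the end of the rTMS treatment", with p < 0.05 and no stated correction. The Discussion frames the question as whether network activity and connectivity "is correlated with the cognitive improvement following the rTMS stimulation".

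Methods 3, Outcomes, makes fMRI a secondary outcome. Methods 1(4), Sample size, gives 45 patients, 15 per site subgroup.

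**The concern.** A seed chosen because it appears to differ will tend to differ again when tested on the same scans, even if no true effect exists. No threshold, atlas or blinded rule is given for the visual step, so it could not be reproduced or audited. The later correction takes the seed as given. It controls error over the voxels of one map and knows nothing of the candidate regions that were looked at and passed over.

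The neuroimaging mechanism is a stated aim of the trial. If the seeds are chosen this way, a significant DMN, DAN or CEN result cannot be told apart from a product of the selection.

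The correlations add a smaller problem. Many pairs of imaging measure and score are possible, each at p < 0.05, and the sentence can be read as setting imaging change against score level. That would not answer whether network change goes with cognitive gain.

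**Working it through.** **Do selection and testing share data?** The ICA is run on the three groups, and the maps are tested in the three site subgroups. Methods 3, Outcomes, places scans at baseline and end of treatment; Methods 1(3), Participant timeline, also lists fMRI at W17. On either account every scan comes from the same 45 patients (9 × 5 = 3 × 15 = 45), and no separate selection sample is described.

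**Is dependence between the two steps plausible?** The strength of a region in an ICA network and its seed correlation with that network are both measures of coupling from the same time series. They are not the same quantity, but they should be positively related.

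**Illustrative size.** The protocol gives no error rate to reproduce. From the document: three groups of 15, one-way ANOVA. Assumed: K candidate regions, and correlation ρ between the inspected measure X and the tested measure Y. Under the null:

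- draw X for K independent regions and pick the region with the largest spread of group means;
- set Y = ρX + √(1 − ρ²)·noise for that region;
- test Y by F(2, 42) at 0.05 (critical value 3.22).

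Rejection rates from 40,000 null trials per setting:

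| K | ρ = 0 | ρ = 0.5 | ρ = 0.8 | ρ = 1.0 |
|---|---|---|---|---|
| 5 | 5% | 10% | 16% | 21% |
| 10 | 5% | 12% | 24% | 37% |
| 20 | 5% | 14% | 33% | 57% |

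An exact check is available at ρ = 1 if the region is picked by its F statistic instead: the rate is then 1 − 0.95^K, which for K = 10 is 1 − 0.599 = 40%, and the simulation gives 40%. The ρ = 0 column shows that seeds chosen independently of the tested contrast restore the nominal level.

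**Correlations.** With m independent null tests at 0.05, the chance of at least one false positive is 1 − 0.95^m, and the expected number is 0.05m.

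- m = 20: five scores × four imaging measures (ALFF and three network FCs). 1 − 0.95^20 = 64%; expected 1.0.
- m = 40: the same at two visits. 1 − 0.95^40 = 87%; expected 2.0.
- m = 48: TMT split into Parts A and B, so 6 × 4 × 2. 1 − 0.95^48 = 91%; expected 2.4.

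The tests will not be independent. With a common correlation of 0.5 between test statistics, simulation gives about 42% for m = 20 and 57% for m = 40; with 0.8, about 23% and 28%.

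**The case against.** **The simulated rates are not those of the planned test.** A reader might take 12% to 37% as the true type I error of the FC analysis. The documents do not support that. The plan tests whole-brain maps with GRF correction; the simulation tests one scalar at an uncorrected 0.05, and K and ρ are nowhere stated. The ρ = 1 case treats ICA appearance and seed FC as identical, which they are not. If the two were unrelated, the inflation would vanish. This stands: the figures show direction and plausibility only.

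**Which differences are inspected is not stated.** They may be between sites or before versus after treatment. The simulation covers only the between-site ANOVA; the paired tests would be affected differently. This stands as a limit on size. Either contrast is among those tested later, so the circularity remains.

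**The two network sources may not conflict.** A reader might infer a contradiction between the Neurosynth networks and the ICA step. A coherent reading is that Neurosynth defines the networks and ICA extracts them in these patients. The text is unclear, but a contradiction is not shown. On either reading the seeds come from the visual step.

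**The correlation sentence is ambiguous.** It is tempting to say that the plan correlates imaging change with score levels at two visits. The sentence can equally mean baseline-to-end change on both sides, and the Discussion favours that. It needs rewording; an analysis error is not established. Nor is 91% a firm figure, since it needs the TMT split, both visits and independence.

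**The imaging work is secondary and exploratory, and detail may sit in an unseen analysis plan.** This lowers the stakes and covers much of the multiplicity point. It does not cover the visual step, because the article itself fixes that rule.

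**Conclusion.** The concern holds for the seed selection. As written, the FC seeds are chosen subjectively for appearing to differ and are tested in the same patients, and GRF correction does not remove the resulting bias. The secondary connectivity conclusions lean towards false positives by an amount that the document does not allow to be fixed. About 12% to 37% at a nominal 5% is an illustration under 10 assumed regions and ρ from 0.5 to 1.0. The MoCA-BJ and TMT analyses and the choice of optimum parameters do not use the FC seeds and are unaffected.

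The correlation point is secondary: a request for clearer wording and a stated stance on multiplicity. For 20 to 48 tests the chance of at least one false positive is 64% to 91% if independent, and lower if correlated.

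**What to change.** - Define the DMN, DAN and CEN seeds before the imaging data are analysed, from the Neurosynth networks already named in Methods 3(6), by one rule applied to all patients and visits. The rule should say how a seed overlapping infarcted tissue is handled.
- Delete the visual-selection step. ICA may stay as description.
- Reword the correlation sentence in Methods 4 as change in ALFF or FC against change in score, from baseline to end of treatment. List the pairs and apply FDR control over that list, or label the correlations exploratory.

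The cost is wording and a seed-definition step, with no new patients or scans. Some apparent findings will be lost, and fixed seeds may fit lesioned brains less well than seeds placed by inspection.
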